Type 2 diabetes mellitus (T2D) is an increasing global health burden. In 2019, diabetes was the direct cause of 1.5 million deaths worldwide.^10^ In addition to the cost of treatment for T2D and its complications, which is a significant burden for national health services, T2D and other NCDs heavily impact productivity, particularly concerning lost or reduced working days due to illness.^11^ Central and South American countries spend an average of 18.4% of their total health expenditure on diabetes.^12 13^ Diabetes detection and control are primarily the responsibility of the non-private schemes.^14 15^ To date, Argentina’s PHC system has failed to meet this challenge; T2D detection and control coverages are low, and those in treatment often bypass PHC for secondary facilities.^16^ Of the estimated 12.7% of the national population living with T2D, only 50% are aware of living with their diagnosis, and only 40% of these individuals have achieved metabolic control (HbA1c <7%), leaving 80% of cases uncontrolled.^17 18^

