#### Sample size

Based on preliminary data from the diagnostic phase and published literature, the baseline rate of achievement for the composite primary outcome (glycaemic control (HbA1c <8%); blood pressure control (<140/90 mm Hg); and use of statins (statin prescription) -limited to patients ≥40 years-) in the control group is estimated at 30%. The intervention is expected to improve this to ≥50% (absolute effect size of 20%). We have calculated the sample size considering a parallel cluster randomised trial with a cohort design, including baseline and follow-up assessments. The trial is powered at 80% to detect an absolute difference of 20 percentage points between the control group (30%) and the intervention group (50%) on the composite primary outcome, assuming a two-sided significance level of 5%. The design includes six clusters per arm (12 in total) and accounts for the correlation structure of repeated measures using a two-period decay model. Specifically, we assumed an intracluster correlation coefficient (ICC) of 0.05, a cluster autocorrelation of 0.5, and an individual autocorrelation of 0.6. Standard errors were adjusted using a t-distribution to account for the small number of clusters. Based on these parameters, the required sample size before adjusting for attrition is 312 individuals (26 per cluster). Applying an attrition inflation factor of 1.25 (to allow for 20% loss to follow-up), the final sample size increases to 396 individuals (33 per cluster, 198 per arm).

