#### Outcomes

The primary outcome will be a composite outcome including glycaemic control (HbA1c <8%); blood pressure control (<140/90 mm Hg); and use of statins (statin prescription) limited to patients ≥40 years. The source to obtain this data will be routine clinical records.

Secondary outcomes measured through participant questionnaires include user-reported quality of care (key secondary outcome), PHC engagement, system competence, patient confidence in the health system, inequities in outcomes and patient empowerment. User-reported Quality of Care is the overall rating of quality of care from enrolled patients, categorised as ‘excellent or very good’ versus ‘good’ or worse. PHC engagement is measured as the percentage of visits conducted at the PHC level during the data collection period, with positive engagement defined as ≥75% of all non-urgent ambulatory visits.^31^ System competence is defined as ≥75% of enrolled patients per site adhering to the complete set of selected diabetes prevention recommendations from national and provincial guidelines: annual eye exam, yearly foot exam, annual kidney function assessment, annual blood pressure measurement and biannual HbA1c measurement during the follow-up period. Patient confidence in the health system is measured by the combination of three aspects in the e-Cohort survey: health security, endorsement of the current system and trajectory.^32^ Security: We will calculate the percentage of respondents answering ‘somewhat’ or ‘very confident’ to ‘How confident are you that you would receive good quality healthcare if you became very sick?’ and ‘that you could afford the healthcare you needed if you became very sick?’. Confidence: The proportion of respondents indicates that in the past 2 years, the health system has been improving (vs staying the same or getting worse). Endorsement is indicated by agreement that the system works well and needs only minor reforms (vs significant changes needed or need to be completely rebuilt). To assess inequities, we will explore gender, migration status, education and income as potential variables related to underperformance in primary outcomes. Finally, we will measure patient empowerment using the Diabetes Empowerment Scale. This instrument is free and easy to use and has been adapted and validated in its Spanish version.^33^

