We will use multiple approaches to address missing data. For clinical outcomes, those with missing outcome data will be considered as not achieving the composite outcome for primary analyses, given the lack of evidence of disease control. We will conduct a sensitivity analysis using inverse probability weights calculated from clinical and participant data to reweight the complete data sample to the total patient population. Inverse weights provide valid estimates of the full sample estimate if the assumption of missing at random is met. We will apply the same approach for secondary outcomes. Based on experience with the eCohort methodology, we anticipate high response rates and largely complete responses within the survey. In the event of greater than anticipated missingness within surveys (eg, skipped items), we will conduct an additional analysis using multiple imputation approaches to robustly impute missing responses.^36^

Planned subgroup analyses will explore the potential differential effects of the intervention by gender, migrant status, income and educational level (effect modifiers). This will indicate whether the intervention contributes to reducing inequalities in care. Subgroup analyses will be exploratory. To evaluate inequalities, we will estimate the slope index of inequality and the absolute gradient of inequality across income groups and educational attainment to quantify the absolute inequality in each outcome within the sample in each arm. All analyses will be performed using R V.4.3.1^37^

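### The 1.25 attrition inflation assumes lost patients leave the analysis, but the primary rule keeps them as failures; at 20% missing, power is about 68%, and uneven recording would favour the better-recorded arm

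*Protocol article*

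**What the plan says.** **Sample size.** "The trial is powered at 80% to detect an absolute difference of 20 percentage points". The assumed rates are 30% under control and 50% under the intervention, tested two-sided at the 5% level. With six clusters per arm, this gives 312 patients (26 per cluster) before attrition. The section continues: "Applying an attrition inflation factor of 1.25 (to allow for 20% loss to follow-up"), which leads to 396 patients, 33 per cluster. It does not mention how missing outcomes are scored.

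**Data analysis.** For the clinical composite, "those with missing outcome data will be considered as not achieving the composite outcome for primary analyses"; the reason given is that there is no evidence of control. Inverse-probability weighting of the complete data, valid under missing at random, is a sensitivity analysis. After the weighting sentences comes: "We will apply the same approach for secondary outcomes".

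**Outcomes.** For the composite: "The source to obtain this data will be routine clinical records". The same section makes use of primary care, yearly blood pressure measurement and twice-yearly HbA1c measurement parts of secondary outcomes. The Introduction says of Argentina that "those in treatment often bypass PHC for secondary facilities". The Data analysis section expects service use to rise in the intervention arm.

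**The concern.** There are two separate problems.

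1. *Dilution.* Inflating the sample replaces patients who leave the analysis. It does not repair an effect that shrinks because missing patients are counted as failures in both arms. The stated 80% power then does not describe the primary analysis.

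2. *Recording bias.* Scoring missing as failure is conservative only when missingness does not favour the intervention. Here the outcome comes from routine records, and the care model aims to increase visits and measurements. If records become more complete in intervention centres, some patients move from failure to success without any change in disease control. Under Procedures in Phase III, control clusters receive the package if it proves effective, so a biased primary result would have consequences.

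**Working it through.** **Inputs (Sample size section).** Two-sided alpha 0.05; 30% against 50%; 6 clusters per arm; ICC 0.05; cluster autocorrelation (CAC) 0.5; individual autocorrelation (IAC) 0.6; t-distribution, degrees of freedom not stated; 26 per cluster before and 33 after inflation.

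**Formula.** For m patients per cluster with a baseline and a follow-up measurement:

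- DE = 1 + (m − 1) × ICC
- r = [m × ICC × CAC + (1 − ICC) × IAC] / DE
- SE² = [p1(1 − p1) + p2(1 − p2)] / (6m) × DE × (1 − r²)
- power from the noncentral t-distribution with noncentrality |p2 − p1| / SE

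**Step 1: reproduce the plan.** At m = 26, DE = 2.25, r = 0.542 and DE(1 − r²) = 1.589. SE = √(0.46/156 × 1.589) = 0.0684 and 0.20/0.0684 = 2.92. Power is 79.8% with 22 df (24 cluster-periods minus 2) and 75.0% with 10 df (12 clusters minus 2). The stated 80% therefore matches 22 df. The inflation is 26 × 1.25 = 32.5, rounded up to 33, and 33 × 12 = 396.

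**Step 2: what the inflation buys.** If 20% leave the analysis, 33 × 0.8 = 26.4 per cluster remain at 30% against 50%. Power is 80.0% (22 df). The factor fits an analysis of patients with data.

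**Step 3: apply the primary rule.** Assume the same missing fraction d in both arms, unrelated to true control status. All 33 per cluster stay in, and each rate is multiplied by (1 − d). At d = 0.20 the rates are 0.30 × 0.8 = 0.24 and 0.50 × 0.8 = 0.40. With DE = 2.60, r = 0.537 and DE(1 − r²) = 1.852, SE = √[(0.1824 + 0.2400)/198 × 1.852] = 0.0628 and 0.16/0.0628 = 2.55.

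| Missing in each arm | Expected rates | Difference | Power, 22 df | Power, 10 df |
|---|---|---|---|---|
| 5% | 28.5% / 47.5% | 19 points | 79.7% | 74.9% |
| 10% | 27% / 45% | 18 points | 76.1% | 71.1% |
| 20% | 24% / 40% | 16 points | 68.2% | 63.2% |

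Like for like, at 20% missing, the loss is 80% to 68% (22 df) or 75% to 63% (10 df). A shifted central t gives slightly lower values at 20% (67.9% and 62.1%). With that approximation and 22 df, regaining 80% at 20% missing takes about 129 per cluster (129 × 12 = 1,548 patients), so modest extra recruitment is no remedy.

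**Step 4: unequal recording, a separate scenario.** The protocol gives no missing rates by arm; those below are illustrative. With no true effect and a true rate of 30% in both arms, the expected false difference is 0.30 × (missing in control − missing in intervention):

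- 20% against 10%: 0.30 × 0.10 = 3 points in favour of the intervention. The chance of a significant result in its favour is about 6.5% to 7% (22 df, by the two t methods), against a nominal 2.5%.
- 30% against 10%: 0.30 × 0.20 = 6 points, and about 15% to 16.5%.

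**The case against.** The strongest reply is that 20% missing is not given for this outcome. The 20% is loss to follow-up. Follow-up contact runs through telephone surveys and an in-person endline questionnaire, whereas the composite is extracted from records for all consenting patients. Someone lost to surveys may still have recorded values, and one recorded failing component settles the composite. This stands: at 5% missing, power is about 80%, as planned. The protocol also does not say whether the 30% already counted unrecorded values as failures. If it did, there would be no such dilution, although the attrition inflation suggests rates among observed patients.

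Recording bias is plausible but unmeasured. The statement about bypassing concerns the country in general, the cohort must receive care at participating centres, and trained data collectors work at each centre with a standardised system. These points lessen the risk but do not remove it, because a collector cannot extract a test that was not done. The weighted sensitivity analysis could expose the bias under missing at random, but it leaves the primary result as it is. Patients attending elsewhere may also breach missing at random, so the choice of primary analysis is partly a trade-off.

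Three stronger readings are tempting and not supported:

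- *The difference shrinks to 16 points and the intervention is also credited for recording.* The first needs equal missingness and the second unequal. With a true 30% against 50% and 20% against 10% missing, the observed rates are 24% and 45%, a 21-point difference.
- *The rule by itself brings power to 63%.* That figure includes the step from 22 to 10 df. Within either choice the rule costs about 12 points.
- *Missing-as-failure is extended to the survey outcomes.* The sentence on secondary outcomes directly follows the weighting sentences and may refer only to them. It is ambiguous and no more.

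**Conclusion.** The point holds in conditional form. The Sample size and Data analysis sections treat lost patients in opposite ways, and the 80% power statement belongs to an analysis that is not the primary one. The 12-point loss of power at 20% missing rests on four assumptions: equal missingness in both arms, missingness unrelated to true control, 30% and 50% as rates among patients with data, and correlations as planned. A lower individual autocorrelation under the failure rule would reduce power further. Recording bias of 3 to 6 points is a different scenario. Its direction follows from the rule and from the protocol's own aims if intervention records are fuller, but its size rests on assumed missing rates. The documents do not show that either scenario will occur, only that the plan does not allow for them.

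**What to change.** 1. Restate power under the failure rule with 33 per cluster over a range of missingness (about 80% at 5%, 76% at 10%, 68% at 20%, with 22 df), and state the degrees of freedom used.
2. State whether the 30% already counts unrecorded values as failures.
3. Commit to reporting missingness by arm and by component (HbA1c, blood pressure, statin prescription).
4. Preferably, make the planned inverse-probability-weighted analysis primary, using baseline and interim record values, or report it with equal prominence. Keep missing-as-failure as a sensitivity analysis.
5. Clarify that the shared approach for secondary outcomes means the weighting and not missing-as-failure.

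The cost is a revised power statement, some added text and perhaps a reordering of analyses already planned; no new data are needed. The downside of item 4 is reliance on missing at random, which patients attending elsewhere could violate; the retained failure analysis shows how far the result depends on it. The changes should be settled before outcome data are seen by arm.

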## Ethics and dissemination

All study activities will comply with national and international ethics guidelines, presenting minimal risk to participants. The protocol was submitted and approved by the local independent ethics committee at the Mendoza Ministry of Health (CoPEIS—Consejo Provincial de Evaluación ética en investigación). Facility-level permission will be obtained for participation and sharing of deidentified data. Written informed consent will be required from study participants (patients with T2D who meet the eligibility criteria), who will receive information on the study’s purpose, procedures, risks and benefits. Evaluation forms, surveys and records will use coded identifiers to ensure confidentiality. Records will be securely stored, and clinical information will only be released with written participant permission or for regulatory monitoring.

Dissemination activities and outputs will include writing and submitting manuscripts for publication; writing policy briefs to support strategy implementation in other regions or countries; and tailoring outputs for patients, clinicians and researchers. We anticipate that improvements in disease management and patient experience will have clinical and economic benefits related to reduced usage of secondary-level and tertiary-level facilities, lower cost per visit and a reduced number of clinical events related to diabetes. On a larger scale, this project constitutes one of the first experiences in SDR for NCDs, and its findings will be informative for future work in this line of research and health policy worldwide with a particular focus on LMICs.
